**Methods/design:**

This study is a randomized, sham-controlled, patient- and assessor-blinded trial and aims to evaluate the effect of OA in women with PMOP. We will recruit 104 women aged 45–70 years with a diagnosis of PMOP. Participants will be randomly allocated in a 1:1 ratio to the OA group and the sham acupuncture (SA) group. Both groups will receive real herbal medicine treatment as a basic treatment twice a day for 3 months, the OA group receives real acupuncture treatment and the SA group receives placebo acupuncture treatment (non-penetrating, sham skin-needle therapy, sham cupping). All patients will receive acupuncture treatment twice per week for 3 months. The primary outcome is bone mineral density (BMD) and the secondary outcomes include estradiol (E2), follicle-stimulating hormone (FSH), bone gla protein (BGP), bone alkaline phosphatase (BALP), total antioxidant capacity (TAC), advanced oxidation protein products (AOPP), PPARγ, β-catenin, FoxO3a levels, visual analog pain scale score (VAS), Traditional Chinese medicine (TCM) syndrome scores and quality of daily life score (QOL). Outcome measures will be collected at baseline, middle of the treatment (1.5 months), the end of treatment (3 months). The present protocol followed the SPIRIT guidelines and fulfills the SPIRIT Checklist.

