### Sample size and blinding

According to the preliminary research [15], we hypothesize that the effective rate after OA is 77.8% and the effective rate after SA is 50%. The equation that we used for this was *α* = 0.05, *β* = 0.20 and we determined that a sample size of 42 patients in each group would be sufficient to detect the statistical difference between the two groups, allowing for a 20% withdrawal rate. We will plan to enroll a total of 104 participants with 52 participants in each group. According to the random number sequence generated by computer, the patients will be randomly divided into either the OA group or the SA group in a 1:1 ratio.

The participants, outcome assessors, study monitors, data managers, and statisticians will be blinded to treatment allocation. If possible, the study participants will be advised to avoid discussing the investigational treatments with other participants. Blinding will be maintained until the 104 participants have completed the study. The success of double-blinding will be assessed at the final visit. Due to the special nature of acupuncture, acupuncturists cannot be blinded to the treatment. The database will then be locked. An emergency code for each individual has been provided to the study researchers and will be disclosed only if it must be known whether a patient is receiving acupuncture treatment or SA in order to manage a serious adverse event.

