### Outcome measures

Outcomes will be collected at baseline, the middle of treatment, after treatment, and follow-up 6 months after the completion of the treatment. The overview of the outcome measurement at the different time points is shown in Table 3.

**Table 3 Tab3:** Overview of study visits

		Study period						
		Enrollment	Allocation	Post allocation			Close out	Follow-up
	Time point (month)	− 1	0	1	2	3		6
Preparation	Enrollment							
	Informed consent	√						
	Eligibility screen	√						
	Allocation		√					
Intervention	OA			√	√	√		
	SA			√	√	√		
Assessment	Liver function Kidney function	√						
	T; BP; P; R	√		√	√	√		
	BMD	√						√
	E2; FSH	√						
	BGP; BALP	√						
	TAC; AOPP	√						
	FoxO3a; β-catenin PPARγ	√						
	VAS	√		√	√	√		√
	TCM syndrome	√			√			
	QOL	√			√			
	Adverse events						√	
	Data analysis						√	
	Fracture rate							√

*T* body temperature, *BP* blood pressure, *P* pulse rate, *R* respiration rate, *OA*, *SA*, *QOL* quality of life, *TCM* traditional Chinese Medicine, *VAS* visual analog scale, *PPAR*, *E2*, *TAC*, *AOPP*, *BGP*, *BALP*, *BMD*, *FSH*

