### Primary outcome

The primary outcome is BMD. BMD is measured using dual-energy x-ray (DEXA) absorptiometry (DMS, Paris, France; model: CHALLENGER C 313). A BMD measurement of the lumbar vertebrae (L1–L4) in the two groups will be measured before and after treatment.

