### Data management

Researchers who have read and understood the standard operating procedures will obtain written consent and collect and manage the study data from the participants, who will be given ongoing encouragement to complete the study. They are telephoned in advanced of each visit and the importance of taking the investigational treatments at the correct times is reinforced. If a participant needs to be withdrawn from the study, the scheduled tests are still performed at the final study visit if the participant is agreeable. If a follow-up investigation is required, researchers will contact the participant by telephone as necessary. After the end of the trial, data entry will be by double entry, and matching will be conducted after inconsistent data has been reviewed. When the data is matched, a data clarification form will be completed and validated.

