### Data analysis

The analysis data set will consist of an intention-to-treat data set, a per-protocol (PP) data set, and a safety data set. The intention-to-treat data set will include all subjects assigned to each group. The PP data set will include only participants who adhered to the study protocol and completed the clinical study. The minimum compliance rate for participants taking the acupuncture treatments in the PP data set is 80%. The safety data set will include any participants who were randomly assigned to, and received, at least 1.5 months of the acupuncture treatments. The intention-to-treat analysis will be the primary analysis and will be compared with the PP analysis in a sensitivity analysis. The last-observation-carried-forward method will be used to manage missing data.

All collected data results were compiled using the SPSS 21.0 statistical software package, and collated, checked and statistically analyzed. The comparison between the data groups was performed by using a *χ*^2^ test, and the measurement data was consistent with the normal distribution and the homogeneity of the variance. The mean ± standard deviation ($$\overline{\mathrm{x}}\pm \mathrm{S}$$) indicates that the rank-sum test is used for comparison between grade data sets that do not satisfy the normal distribution and the homogeneity of the variance. *P* < 0.05 was significant for the difference. The variance analysis will be performed for the difference between the two groups and within the group. We will perform a regression analysis to examine the causal relationship between the E2, TAC and β-catenin, and the primary outcome. The statisticians who are independent of the research team will conduct the data analysis.

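### Last observation carried forward on the primary outcome enters a woman without the post-treatment BMD scan at her baseline value, which biases the treatment effect, and no planned analysis tests this

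*Protocol article*

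**What the plan says.** All references are to the protocol article.

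- **Missing data (Data analysis).** "The last-observation-carried-forward method will be used to manage missing data". No outcome is exempted. The intention-to-treat set of all assigned subjects is primary, and a per-protocol comparison is the only sensitivity analysis named.
- **Primary outcome.** "The primary outcome is BMD", and "A BMD measurement of the lumbar vertebrae (L1–L4) in the two groups will be measured before and after treatment".
- **Table 3 (Outcome measures).** BMD is ticked twice, at enrolment and once later. The later tick stands in the 6-month follow-up column, not at month 3.
- **General timing (Outcome measures).** "Outcomes will be collected at baseline, the middle of treatment, after treatment, and follow-up 6 months after the completion of the treatment". The abstract also mentions a mid-treatment collection at 1.5 months. Neither text names BMD in that context.
- **Withdrawal.** The sample size was set "allowing for a 20% withdrawal rate". Under Data management, for a withdrawn participant, "the scheduled tests are still performed at the final study visit if the participant is agreeable".

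**The concern.** Carrying the last observation forward needs a post-baseline observation to carry. The BMD-specific text and Table 3 both provide a single post-baseline measurement. When it is missing, the rule becomes baseline carried forward, and the participant contributes no change whatever her treatment did.

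This concerns the primary estimate. If the shares missing are equal, any true difference is diluted. If they differ by arm and both arms change on average, part of that common change appears as a treatment difference. A common change is possible here: the Introduction describes bone loss after menopause, and both arms receive herbal medicine. The per-protocol set keeps only adherent completers, so it swaps the zero-change assumption for selection and does not examine that assumption.

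**Working it through.** **The plan's own figure.** The sample size serves here only to fix n and a reference effect, because it rests on a binary effective rate and not on BMD. For 77.8% v 50%, two-sided 0.05, 80% power, unpooled variance:

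n = 2.802² × (0.778×0.222 + 0.5×0.5) / 0.278² = 42.9 per arm, close to the stated 42. Then 42/0.8 = 52.5, against the stated 52.

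**Assumptions not in the documents.** BMD change has SD 1 in each arm, scans are missing at random with share d, and there are 52 per arm. The reference difference is what 42 per arm detects with 80% power: 2.802 × √(2/42) = 0.611 SD.

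**Formulas.** Under the rule, an arm with true mean change μ has
- mean (1−d)μ
- variance (1−d) + d(1−d)μ²

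**Case 1: 20% missing in both arms, true difference 0.611 (means 0.611 and 0).**
- Women imputed: 0.2 × 52 ≈ 10 per arm.
- Estimate: 0.8 × 0.611 = 0.489, a 20% attenuation.
- Variances: 0.8 + 0.16×0.611² = 0.860, and 0.800. SE = √((0.860 + 0.800)/52) = 0.179.
- Bias in SE units: (0.611 − 0.489)/0.179 = 0.68. Coverage of the true difference: Φ(1.96 − 0.68) − Φ(−1.96 − 0.68) ≈ 0.895. Splitting the difference as +0.306 and −0.306 gives 0.894.
- Power: 78% to 79%. Observed scans only: SE = √(2/41.6) = 0.219, power 79.6%.
- With no true difference and equal missingness, type I error is 5%.

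With 10% missing in both arms the estimate is 0.550.

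**Is the SE itself wrong?** No. A simulation of Case 1 gave a sampling SD of 0.178 and a mean estimated SE of 0.178. The coverage loss comes from the bias.

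**Case 2: no true difference, common mean change μ, 10% v 30% missing.** The spurious difference is (0.9 − 0.7)μ = 0.2μ.

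| Common change μ (SD) | Spurious difference (SD) | SE | Type I error |
|---|---|---|---|
| 0 | 0 | 0.175 | 5.0% |
| 0.1 | 0.02 | 0.176 | 5.1% |
| 0.5 | 0.10 | 0.179 | 8.6% |
| 1.0 | 0.20 | 0.191 | 18.2% |

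**Case 3: true difference 0.611, 10% v 30% missing.** The estimate lies between 0.43 and 0.55 SD and power between 66% and 87%, depending on which arm loses more scans.

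**The case against.** Several points on the other side are sound and limit the finding.

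- **Not every withdrawal is affected.** A reader might infer that each dropout is entered as no change. Data management keeps final-visit tests for withdrawn participants who agree, so only women without the post-treatment scan are affected. The 20% is a planning allowance for withdrawals, not a forecast of missing scans.
- **The standard error is not miscalculated.** A reader might infer from 0.179 v 0.219 that the imputed zeros make the SE false. These are the SEs of two different estimators, and each is right for its own. The interval is in the wrong place.
- **The change scale is not fixed.** The Data analysis section speaks only of an analysis of variance between and within groups. If post-treatment levels are compared, a carried-forward baseline has ordinary between-patient spread, and the variance formula above does not apply. The attenuation does: baseline means are equal in expectation, so the expected difference is still multiplied by (1−d) when missingness is equal.
- **Serious type I inflation needs two conditions together.** Missingness must differ by arm, and the common change must be sizeable. The documents give neither. The Introduction's statement on bone loss covers 5 years, not 3 months, and participants are blinded.
- **A mid-treatment scan is possible.** The general timing statements could be read to include BMD. The BMD-specific text and Table 3 do not show such a scan, and it would not help women who leave before it. Those who leave later would be entered at a half-course value.
- **The details could sit in an analysis plan.** That would answer an omission. Here a method is stated, and it is the wrong one for this outcome.

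**Conclusion.** The point holds in this limited form. The stated rule, applied to an outcome with one post-baseline measurement, places participants without that scan at baseline and biases the primary estimate.

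With equal missingness the effect is diluted in proportion to the missing share: 20% at the upper scenario, with about 89% coverage, but no loss of type I error control and almost no loss of power. With unequal missingness the bias can run either way. Type I error then ranges from about 5% to 18% over the assumed common changes of 0.1 to 1 SD at 10% v 30% missing. If the mean change is zero in both arms there is no bias.

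All sizes are in assumed SD units and cannot be converted to BMD units from the documents. They do not support a claim that the trial's false-positive rate is inflated in general. The rule should still be changed before database lock, because it governs the primary result and no planned analysis would reveal the problem.

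**What to change.** 1. Remove last observation carried forward for the primary outcome. Compare post-treatment BMD by ANCOVA adjusted for baseline BMD, in all randomised participants, using the final-visit scans of withdrawn participants.
2. Impute scans that are truly missing by multiple imputation within arm, from baseline BMD, age, site and other collected covariates.
3. Add a delta-adjusted sensitivity analysis that shifts the imputed values, by different amounts in each arm, to show how far the conclusion depends on the missing-data assumption.
4. For repeatedly measured outcomes such as VAS, use a mixed model for repeated measures instead of carrying values forward.
5. Reconcile the timing of the BMD scan. The Primary outcome section places it after treatment, Table 3 ticks it at 6 months, and the Blood testing section describes that follow-up as a telephone call. State also whether any mid-treatment scan is planned.

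The cost is a few sentences, a little more analysis work and a somewhat wider interval (in Case 1, observed scans before any baseline adjustment: 0.219/0.179, about 1.2 times as wide). No extra visit or participant is needed.

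### The Data analysis section lets checks of the trial's own data decide between a mean-based test and the rank-sum test for BMD, and wrongly treats unequal variance as a reason for ranks

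*Protocol article*

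**What the plan says.** Under Primary outcome, the protocol states that "The primary outcome is BMD", measured at L1–L4 before and after treatment. The Data analysis section then describes the methods in a few sentences:

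- A chi-square test is named for comparison between groups.
- In the same sentence comes the condition that "the measurement data was consistent with the normal distribution and the homogeneity of the variance". No t-test is named.
- The next sentence, which opens with the mean and SD notation, says that the "rank-sum test is used for comparison between grade data sets that do not satisfy the normal distribution and the homogeneity of the variance".
- Separately, "The variance analysis will be performed for the difference between the two groups and within the group".
- The threshold is P "< 0.05 was significant for the difference", with no sidedness given.
- "The last-observation-carried-forward method will be used to manage missing data".

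No sentence ties any one of these tests to BMD.

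**The concern.** Normality and equal variance are conditions that one checks on continuous data. Ordinal grades would go to a rank test whatever such checks showed. So the section reads as a check-then-choose rule: means if both conditions hold, ranks if they fail. Two things follow.

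First, unequal variance becomes a stated trigger for the rank-sum test. That test holds its level when the two distributions are identical. When spreads differ it does not test equality of means, and its error rate for that null can drift.

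Second, the data choose the question. On one branch the trial reports a mean difference in BMD. On the other it reports a rank comparison with no BMD difference attached. For the primary outcome, that choice would be made only after the results are seen.

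The missing-data rule makes the switch more likely. BMD is measured before and after treatment. If a woman without a second scan has her baseline value carried forward, her change score is exactly zero. A block of exact zeros tends to fail a normality check even when the completers' changes are normal.

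**Working it through.** **The plan's own figure.** The sample size was reproduced first, to see whether it reveals the primary test. Inputs from Sample size and blinding: rates of 77.8% and 50%, α = 0.05, power 0.80, 20% withdrawal. With unpooled variance and a two-sided test:

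n = (1.960 + 0.842)² × (0.778 × 0.222 + 0.5 × 0.5) / (0.278)² = 42.9

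This rounds up to 43 against the stated 42. For withdrawal, 42 / 0.8 = 52.5 against the stated 52. Both agree within rounding. But the calculation concerns an effective rate, not BMD, so it does not show how BMD is to be tested.

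**The rule that was simulated.** Shapiro–Wilk in each arm and Levene's test, each at 5%. If all three pass, the two-group t-test (equivalent to ANOVA); otherwise the rank-sum test. The comparator is Welch's test with no preliminary checks. True means are equal and tests are two-sided at 5%, with 20,000 trials per scenario. The protocol names no preliminary tests and gives no SD or distribution for BMD, so these are assumptions shown over a range.

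**Type I error of the rule, normal data:**

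| SD ratio | 52 v 52 | 42 v 52, larger SD in smaller arm | 52 v 42, larger SD in larger arm |
|---|---|---|---|
| 1 | 5.1% | – | – |
| 1.5 | 5.2% | 5.7% | 4.6% |
| 2 | 5.5% | 6.4% | 5.1% |
| 3 | 7.0% | 7.9% | 5.6% |

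Separate runs at 52 per arm gave 4.8–6.0% up to ratio 2 and 6.8–7.4% at ratio 3. Welch stayed between 4.8% and 5.3% in every scenario of the main run.

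**Same distribution in both arms.** With identical skewed (gamma) data the rule rejects in 4.9% of trials; with identical normal data, in 5.1–5.2%. The level holds.

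**How often the rule switches.** With ideal normal data and equal SDs, three checks at 5% would fail by chance in about 1 − 0.95³ = 14% of trials if they were independent. The simulations give 13–14%.

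**Carried-forward zeros.** Assume 52 per arm, 20% of change scores exactly zero, and a true effect of 0.62 SD among the others. The rule goes to ranks in about 70% of trials. Its power is 75–76%, against 78–79% for Welch, a loss of about 3 points. With no treatment effect, the zeros alone do not inflate the error (4.8%).

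**The case against.** The strongest reply is that the rank-sum sentence speaks of grade data, and the trial has such data: the 0/2/4/6 symptom grades in Table 5 and the banded quality-of-life score in Table 6. On that reading BMD, as measurement data, falls under the variance analysis, which is stated without conditions. In part this stands. The application to BMD is the natural reading of a garbled sentence, not an explicit statement. But if only ordinal data were meant, normality and equal variance would have no role in the sentence, and it would still need correcting. The variance-analysis sentence names no outcome and does not say whether it overrides the rank-sum rule.

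A second reply is that test selection is commonly left to an analysis plan. That would answer an omission. Here the article states a rule, and the rule is faulty.

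A third is that the numbers are small for BMD. This stands. Nothing in the documents suggests a twofold or threefold SD difference between arms that share the same herbal treatment. The 20% of zeros is an upper-end assumption, because Data management says that withdrawn women still have the final tests if they agree.

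A reader might infer a stronger point: that skewed hormone and serum markers would give grossly inflated error. With lognormal data, equal means and SD ratios of about 1.6 and 1.9, the rule does reject in about 17% and 30% of trials. The documents do not support that as a case against the rule. Welch's test on logged values, a usual choice for such markers, rejects in 17.5% and 30.5%. The medians in those scenarios differ by about 10% and 15%, so the arms do differ. When both lognormal arms are identical, the rule holds its level (4.6–5.3%). Under a multiplicative shift, Welch on the raw scale has less power than the rule (63% v 68%). For those markers the choice is a trade-off.

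**Conclusion.** The point holds in a limited form. As naturally read, the section lets the data choose the test and the effect measure for the primary outcome, and it gives unequal variance as a reason for ranks, which is wrong. The cost in error rate is modest: about 5–6% at 52 per arm for normal data up to SD ratio 2, about 7% at ratio 3, nearly 8% at that ratio with 42 v 52 and the larger SD in the smaller arm, and nominal when the arms share one distribution.

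The firmer harms are the unfixed primary test and effect measure, and a power loss of about 3 points if roughly 20% of change scores are carried-forward zeros. These figures rest on assumed SD ratios, assumed preliminary tests at 5%, and, for the power loss, analysis of change scores. The documents state none of these. It would go too far to say that the BMD result is likely to be a false positive, or that the hormone and serum-marker analyses are invalid.

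**What to change.** In Data analysis:

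1. Name one mean-based comparison for BMD that allows unequal variances: Welch's test, or a regression model with robust standard errors. State that it is used whatever any distribution check shows.
2. Report the mean difference in BMD with its 95% CI.
3. Keep the rank-sum test for ordinal grade data and as a supportive analysis, and remove unequal variance as a reason to use it.
4. For secondary markers expected to be skewed, fix the method before unblinding. No particular transformation need be imposed.

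This is a change of wording and needs no new data. The loss of power is negligible if the variances are in fact equal: with equal-SD normal data, Welch and the ordinary t-test gave the same rejection rate in the simulation (both 4.97% at 52 per arm).

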**Fig. 1 Fig1:**
[figure not shown]
Study flow chart

Participants who voluntarily sign the informed consent, and who are eligible for this study, will be assigned randomly to one of two groups (the acupuncture group or the SA group) in a 1:1 allocation. On the consent form, participants will be asked if they agree to the use of their data should they choose to withdraw from the trial. Participants will also be asked for permission for the research team to share any relevant data with people from the Dali University who are taking part in the research or from regulatory authorities, where relevant. The study participants were recruited competitively from two sites of the Acupuncture and Moxibustion Department of Yunnan Province Hospital of TCM and the First Affiliated Hospital of Dali University. A total of 104 postmenopausal women with osteoporosis were recruited via broadcast media, newspapers, posters, and the Internet homepages of the participating hospitals, as well as via advertisements placed in nearby welfare centers.

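### The analysis plan does not fix one primary between-group BMD contrast or say how baseline BMD enters it, and it places within-group tests beside the comparison with sham

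*Protocol article*

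**What the plan says.** The Primary outcome section states "The primary outcome is BMD" and adds that L1–L4 BMD "in the two groups will be measured before and after treatment". A baseline value is therefore planned for every participant.

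The Data analysis section names these methods:

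- For group comparison: "The comparison between the data groups was performed by using a" chi-square test.
- For data that fail the assumptions: "the rank-sum test is used for comparison between grade data sets that do not satisfy the normal distribution" (and homogeneity of variance).
- An analysis of variance: "The variance analysis will be performed for the difference between the two groups and within the group".
- One regression: "We will perform a regression analysis to examine the causal relationship between the E2, TAC" and β-catenin, and the primary outcome. This is a mechanistic model and does not compare the arms.

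One significance rule, P < 0.05, covers all of these. The section does not say whether the analysis of variance is run on post-treatment values, on change from baseline, or as a repeated-measures model. It also does not say which result answers the primary question.

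The Interventions section gives herbal medicine to both arms, twice a day for 3 months.

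**The concern.** Two things are at stake.

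1. **Precision and a fixed contrast.** BMD over a few months is likely to be strongly correlated with its baseline value. A comparison that leaves baseline out keeps all the between-patient variation and any chance baseline imbalance in the estimate. The wording leaves a post-only, a change-score and a repeated-measures analysis all open after the data are seen.

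2. **Within-group conclusions.** A significant before–after rise in the OA arm could be read as efficacy. The OA arm also takes the herbs, so such a rise cannot be attributed to acupuncture. Only the difference between arms can.

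**Working it through.** **Inputs from the protocol.** From Sample size and blinding: "The equation that we used for this was *α* = 0.05, *β* = 0.20", 42 per group before withdrawals, and effective rates of 77.8% and 50%. Sidedness is not stated; two-sided is assumed here.

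**The plan's own figure.** Two proportions, two-sided, unpooled variance:

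n = (1.960 + 0.842)² × (0.778×0.222 + 0.5×0.5) / 0.278² = 42.9

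That is 43 per group against the stated 42, so the figure essentially reproduces. It rests on a binary effective rate and says nothing about precision for BMD.

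**Assumptions.** The protocol gives neither an SD for BMD nor the correlation ρ between baseline and post-treatment BMD. Results are in SD units with equal SD at both visits, and ρ is assumed over 0.8 to 0.95.

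**Variance of the OA–SA difference, relative to comparing post-treatment values:**

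- Post-treatment values alone: 1
- Change from baseline (for two visits, the same test as the group-by-time term of a repeated-measures ANOVA): 2(1−ρ)
- ANCOVA on baseline: 1−ρ²
- ANCOVA relative to change: (1−ρ²) / [2(1−ρ)] = (1+ρ)/2

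**Detectable difference at 42 per arm, 80% power.** For post-only values, (1.960 + 0.842) × √(2/42) = 0.611 SD by the normal formula, or 0.619 SD with the t distribution (about 0.62). The other designs multiply this by the square root of the relative variance. The table uses the normal formula.

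| ρ (assumed) | Post-only variance ÷ ANCOVA variance | Detectable: post-only | Detectable: change | Detectable: ANCOVA | ANCOVA variance ÷ change variance |
|---|---|---|---|---|---|
| 0.80 | 1/0.36 = 2.8 | 0.611 | 0.387 | 0.367 | 0.90 |
| 0.90 | 1/0.19 = 5.3 | 0.611 | 0.273 | 0.266 | 0.95 |
| 0.95 | 1/0.0975 = 10.3 | 0.611 | 0.193 | 0.191 | 0.975 |

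Power for an illustrative true difference of 0.2 SD is 15% post-only. Across the same ρ range it is 31 to 83% for change and 33 to 84% for ANCOVA.

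The reading of the ANOVA therefore decides the size. Against a post-only analysis the gain from ANCOVA is large. Against change scores it is 2.5 to 10% of the variance.

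**Within-group tests.** Suppose both arms have the same true change, so OA adds nothing to sham, and each within-arm test has power p. With independent arms, the chance that exactly one arm is significant is 2p(1−p):

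- p = 0.3: 2×0.3×0.7 = 42%
- p = 0.5: 2×0.5×0.5 = 50%
- p = 0.8: 2×0.8×0.2 = 32%

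In half of these cases that arm would be OA: 21%, 25% and 16%.

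**When BMD is measured.** The Abstract has outcomes collected up to the end of treatment at 3 months, and Primary outcome says before and after treatment. Table 3, as extracted, ticks BMD only at month −1 and in the follow-up column. The post-treatment value that any model would use is not settled.

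**The case against.** The strongest reply is that the text never says baseline is ignored. A before–after outcome with between-group and within-group comparisons can well mean repeated measures or change scores, and both use baseline. This stands. A reader might infer that the plan discards baseline and so loses most of its precision. The documents do not support that as fact: it holds only under the post-only reading, and ρ is assumed.

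A reader might also infer that chi-square is to be applied to BMD, or that BMD will be switched to a rank test after looking at the data. The sentences are too garbled to show either. They look like a compressed list of tests by data type, and the rank-sum sentence refers to graded data.

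Nor is the absence of a site term an error. The Study design section says "The study participants were recruited competitively from two sites", and no stratification by site is described. Adjusting for site is an option.

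An article may also leave covariates and model form to the full protocol or the analysis plan. That is fair as to detail. It does not cover what the article does state: within-group testing beside the between-group test under one significance rule, with no sign of which decides efficacy.

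Finally, the stated aim is to compare OA with SA, and nowhere does the protocol say that a within-group change will count as efficacy. So the misuse is a risk that the wording leaves open and is not a stated intention.

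**Conclusion.** The point holds as one of ambiguity with a free improvement. The plan collects baseline BMD but does not fix one primary between-group contrast or say how baseline enters it. The loss runs from large (post-only: variance about 2.8 to 10 times that of ANCOVA) to small (change or repeated measures: 2.5 to 10% more precise with ANCOVA), for ρ of 0.8 to 0.95 and equal SDs. Neither ρ nor the SD is in the protocol. Asymptotically ANCOVA is never worse than either, so the recommendation does not depend on which reading was meant.

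The within-group point is the firmer part and does not depend on ρ: with herbal medicine in both arms, a before–after change in one arm cannot show an effect of OA over sham.

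**What to change.** 1. Reconcile the time point of the post-treatment BMD measurement between Table 3, the Abstract and Primary outcome.
2. State the primary analysis as ANCOVA of post-treatment L1–L4 BMD on arm and baseline BMD (site optional), reporting the adjusted OA–SA difference with its 95% CI.
3. Say that this model is used for BMD whatever the distribution checks show. Keep chi-square for categorical data and rank-sum for ordinal data.
4. State that within-group changes are descriptive and support no efficacy claim.

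Items 2 to 4 cost analysis wording only, since baseline BMD is already collected and the recruiting site is known. Item 1 is also wording if the measurement is already made at the time settled on; otherwise the visit schedule has to be corrected too. The choice should be recorded before the data are unblinded.
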